### Routine electronic monitoring of HRQoL duration

Patients clinical and HRQoL data will be monitored for two years from the initiation of sunitinib or pazopanib. Patients will participate in REMOQOL until sunitinib or pazopanib is permanently discontinued due to toxicity, progression or death, and also according to a decision by the investigator, non-compliance with the protocol or loss of follow-up.

All patients included in this study will be able to leave at any time, without having to justify the reason.

After treatment discontinuation, all living patients can choose to continue REMOQOL during the subsequent therapy.

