#### Population analysis

Evaluable patients will be defined as all patients who filled out at least one questionnaire and are still alive or without progressive disease three months after the start of treatment.

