#### Sample size

The following hypotheses will be tested:

H0 (null hypothesis for inefficiency): 60% or fewer patients having good compliance with REMOQOL during the first 12 months following the initiation of treatment will be considered as irrelevant;

H1 (alternative efficiency hypothesis): 80% of patients having good compliance with REMOQOL during the first 12 months following the initiation of treatment is expected.

Considering Fleming’s One-Stage design [32, 33] with a one-sided α type I error rate of 0.05 and a statistical power of 0.90, it will be necessary to include 45 evaluable patients. Due to an estimated 20% drop-out rate and non-evaluable patients, the overall number of patients included will be 56 (28 per treatment group).

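### Monitoring may be ended for non-compliance, and the plan conflicts on whether drop-outs stay evaluable, so the primary compliance proportion can be biased upward

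*Protocol article*

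**What the plan says.** Four sections of the Protocol article bear on this point.

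- **Routine electronic monitoring of HRQoL duration.** Participation in REMOQOL lasts until the TKI is permanently stopped, "and also according to a decision by the investigator, non-compliance with the protocol or loss of follow-up". Patients may also leave whenever they wish.
- **Primary outcome definition.** The outcome is good compliance over the first 12 months among evaluable patients, with a 66% threshold on filled questionnaires. I read the threshold as applying to each patient's own questionnaires.
- **Population analysis.** Evaluable patients are "all patients who filled out at least one questionnaire and are still alive or without progressive disease three months after the start of treatment". Later drop-out is not a reason for being non-evaluable.
- **Sample size.** The null is "60% or fewer patients having good compliance with REMOQOL during the first 12 months following the initiation of treatment will be considered as irrelevant", and "it will be necessary to include 45 evaluable patients". Then: "Due to an estimated 20% drop-out rate and non-evaluable patients, the overall number of patients included will be 56". Drop-outs are thus part of the planned loss from 56 to 45.

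Description of materials and Follow-up assessments tie the questionnaires to every physician visit, the former from TKI start to the end of treatment.

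**The concern.** The trial asks whether patients will keep up questionnaire monitoring, and giving it up is the negative answer. The TKI is the physician's choice and visits follow usual care, so questionnaires are the main thing the protocol adds for the patient. Non-compliance with the protocol therefore overlaps heavily with failure on the primary outcome, and the plan makes it a reason to end the very activity being scored. Investigator decision and loss to follow-up can work the same way.

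Take a patient who stops answering at month 5 while alive, on the TKI and still attending visits. By the Population analysis section that patient will usually be evaluable. By the Sample size section a drop-out belongs to the loss that reduces 56 to 45. And if the patient is kept, it is unclear whether visits after withdrawal count as missed. Removing the patient, or stopping the count at withdrawal, can only help the trial reach its success boundary when those who stop are mainly poor compliers.

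**Working it through.** **Inputs.** Null 0.60, alternative 0.80, "with a one-sided α type I error rate of 0.05 and a statistical power of 0.90", 45 evaluable, 20% allowance and 56 included (Sample size); success at 33 or more of 45 (Analysis of the primary endpoint).

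**Step 1: the plan's own design.** Exact binomial, n = 45, success if X ≥ 33:

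- P(X ≥ 33 | p = 0.60) = 0.0446
- P(X ≥ 33 | p = 0.80) = 0.9005, so β = 0.0995

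This is the smallest exact design meeting the stated error rates, and it reproduces. The printed α of 0.045% is a slip for 0.045, or 4.5%. The inflation 45/0.80 = 56.25 is close to the stated 56.

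**Step 2: removing drop-outs.** Suppose true good compliance is 60% among all included, a share d of the included is removed, and a share s of those removed are non-compliers. The rate among those who remain is

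p_eval = (0.60 − d(1 − s)) / (1 − d).

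The article does not give s, so it is an assumption. At s = 40%, removal is unrelated to compliance. I apply the 33/45 rule throughout, since it is the only rule stated.

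| d | s | p_eval | P(X ≥ 33 of 45) |
|---|---|---|---|
| 20% | 40% | (0.60 − 0.12)/0.80 = 0.600 | 0.0446 |
| 20% | 60% | (0.60 − 0.08)/0.80 = 0.650 | 0.1547 |
| 20% | 80% | (0.60 − 0.04)/0.80 = 0.700 | 0.3802 |
| 20% | 100% | 0.60/0.80 = 0.750 | 0.6748 |
| 10% | 40% | (0.60 − 0.06)/0.90 = 0.600 | 0.0446 |
| 10% | 60% | (0.60 − 0.04)/0.90 = 0.622 | 0.0810 |
| 10% | 80% | (0.60 − 0.02)/0.90 = 0.644 | 0.1371 |
| 10% | 100% | 0.60/0.90 = 0.667 | 0.2167 |

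The s = 100% rows are the upper bound for each removal rate.

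**Step 3: the boundary in counts.** If the 56 − 45 = 11 patients removed hold no good compliers, 33 successes in 45 are 33 of 56 included: 33/56 = 58.9%, below the 60% null.

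**Step 4: stopping the count at withdrawal.** Assume 12 visits in the window. A patient fills 4, misses 2 and leaves monitoring. On a truncated count the score is 4/6 = 66.7%, which passes 66%. On all visits it is 4/12 = 33.3%, which fails. If a quarter of the true non-compliers among the evaluable were reclassified in this way, the rate would be 0.60 + 0.40 × 0.25 = 0.70, and P(X ≥ 33 of 45) = 0.3802. The quarter and the 12 visits are illustrative.

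**Step 5: all 56 as denominator.** Requiring at least 41 of 56 gives α = 0.0278 and power 0.9205 at 80%. Requiring 40 gives α = 0.0517, just above 0.05.

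**The case against.** The strongest reply is that the text never says what the concern fears.

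- **Due questionnaires after withdrawal.** A reader might infer that nothing is due once monitoring ends. The article does not say so. The section on monitoring duration governs participation, not scoring, and the visit-based schedule together with the 12-month window allows later visits to be counted as missed. This stands: the point is open, not decided the wrong way.
- **Leaving the denominator.** A reader might infer that drop-outs are excluded by rule. The Population analysis section is the operative definition and would keep most of them. The 20% is a recruitment allowance, and it must also cover patients who never fill a questionnaire or fail the three-month condition. This stands too, but it leaves the two sections in conflict over drop-outs.
- **What non-compliance means.** It could also cover breaches of eligibility or forbidden drugs. True; the overlap with missed questionnaires is a plausible reading, not a stated definition.
- **Truncation is narrow.** A patient withdrawn for missing questionnaires passes on a truncated count only if already at 66% or above. One more miss (4/7 = 57%) or one fewer filled (3/6 = 50%) fails either way. This stands for non-compliance withdrawals. Voluntary leavers with a good early record are the likelier route.
- **The null is defined among evaluable patients.** Step 2 measures 60% among all included, which is a different population. Fair, but the stated purpose is to learn whether monitoring is feasible on a large scale, which those who give up also inform.
- **Left to the SAP.** Detailed scoring rules often are, and their absence is not the finding. The stated withdrawal reason and the conflict over drop-outs are in the article itself.

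**Conclusion.** The concern holds in a limited form. The article makes an event that overlaps primary-outcome failure a reason to end monitoring, and its sample-size and population sections disagree on whether drop-outs are evaluable. If drop-outs are removed, or their count stops at withdrawal, the primary proportion can be biased upward.

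The size depends on who is lost. For the removal route, with 60% compliance among all included, the chance of a positive conclusion stays at 0.045 when loss is unrelated to compliance. With 20% removed it reaches 0.67 only if every patient removed is a non-complier; with 10% removed that ceiling is 0.22. Intermediate shares are more plausible than either end, but the article gives no figure to choose among them.

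Two stronger conclusions might be drawn and are not supported. The type I error is not shown to be lost: the 33/45 rule keeps its 4.5% for compliance among evaluable patients if these patients are fully scored. Nor does the article say that the secondary missing-data rate would be computed only in patients still taking part; it says that the rate is reported at each measurement time.

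**What to change.** 1. **Routine electronic monitoring of HRQoL duration:** remove questionnaire non-compliance as a reason to end the scored monitoring, or state that ending participation does not end scoring.
2. **Primary outcome definition and Population analysis:** state that evaluable patients who stop questionnaires by choice, investigator decision, non-compliance or loss to follow-up, while alive and on the TKI, stay in the denominator. Physician visits up to TKI discontinuation, death or month 12 count as due and not filled.
3. **Sample size:** limit the 20% allowance to patients who are non-evaluable under the Population analysis definition.
4. **Supporting analysis:** report all 56 included with drop-outs as failures, against at least 41 of 56 (α 0.028, power 0.92). That power supposes 80% compliance among all 56. If 20% were failures by drop-out and 80% of the rest complied, the overall rate would be 0.80 × 0.80 = 64%, so this belongs beside the primary analysis and not in its place.

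These changes concern scoring only and need no extra patients. The cost is a somewhat less favourable estimate, and visit dates are needed for patients who stop answering, subject to their consent to continued data collection.

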### Follow-up assessments

From treatment initiation, clinical, radiological, and biological data will be prospectively collected. Patients will fill out electronic EORTC QLQ-C30 and EuroQoL EQ-5D questionnaires at each physician visit, regardless of the interval between visits. Patients will be monitored for two years from the initiation of sunitinib or pazopanib treatment, according to the schedule of usual medical care. Following cancer progression, the physician and patient have the choice to continue REMOQOL for the subsequent therapy. Any subsequent treatment will be recorded with the date and mode of progression.

### Statistics and data analysis

#### Primary outcome definition

The primary outcome of the QUANARIE trial is the proportion of patients having good compliance with REMOQOL during the first 12 months following treatment initiation, which is defined as at least 66% of patients with filled out questionnaires during follow-up, among the overall evaluable patients.

#### Population analysis

Evaluable patients will be defined as all patients who filled out at least one questionnaire and are still alive or without progressive disease three months after the start of treatment.

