#### Key trial objectives

The primary objective of the QUANARIE study is to evaluate the proportion of patients having good compliance with REMOQOL during the first 12 months of treatment.

The key secondary objectives are the following:To report the number of patients to whom the study was proposed divided by the number of patients initiating sunitinib or pazopanib treatment in each centre;To report the number of patients who agreed to participate in this study as compared with the number of refusals divided by the total number, by centre and by molecule type (sunitinib or pazopanib);To estimate the rate of missing data defined as the numbers of completely or partially filled items by HRQoL questionnaire and for each measurement time. We will consider a questionnaire as filled out if at least 10 items are completed;To Describe the toxicities collected by the physician according to the NCI CTCAE V4 and reported by the patient according to the eight symptomatic dimensions of the QLC-C30 questionnaire and the six supplementary symptomatic dimensions;To evaluate Physicians’ satisfaction regarding the CHES software and REMOQOL by a questionnaire submitted at the end of the inclusion.

The exploratory objectives are the following:To estimate OS, defined as the time from the start of treatment to death;To estimate PFS, defined as the time from the start of treatment to progression or death;To estimate Time to deterioration of HRQoL (TTD): TTD will be defined as the time from the start of treatment to the first significant deterioration (either increase or decrease depending of the scale) in a HRQoL score as compared with the baseline score with no further significant improvement as compared to the baseline score, or death [29, 30]. Pre-specified targeted HRQoL dimensions will be global quality of life (QL), physical functioning (PF), and fatigue (FA). In these dimensions, will be considered as significant a deterioration over time of ten points at least and an improvement of eight points in QL, seven points in PF and nine points in FA [31].

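### Patients who never fill out a questionnaire leave the denominator of the primary compliance proportion, so the result can only be biased toward success

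*Protocol article*

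**What the plan says.** All references are to the protocol article.

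- **Key trial objectives.** The primary objective is "to evaluate the proportion of patients having good compliance with REMOQOL during the first 12 months of treatment". It carries no restriction to users of the system.
- **Primary outcome definition.** The outcome is "at least 66% of patients with filled out questionnaires during follow-up, among the overall evaluable patients". I read good compliance as a patient having filled out at least 66% of the questionnaires due. On that reading, a patient with none has failed.
- **Population analysis.** "Evaluable patients will be defined as all patients who filled out at least one questionnaire" and who "are still alive or without progressive disease three months after the start of treatment".
- **Key trial objectives, missing-data objective.** "We will consider a questionnaire as filled out if at least 10 items are completed". If this also governs the evaluable definition, a patient who only ever answers fewer than 10 items is removed too.
- **Sample size.** The null is "60% or fewer patients having good compliance with REMOQOL during the first 12 months following the initiation of treatment will be considered as irrelevant" and the alternative is "80% of patients having good compliance with REMOQOL during the first 12 months following the initiation of treatment is expected". Both speak of patients, but the design is sized for 45 evaluable ones. Then: "Due to an estimated 20% drop-out rate and non-evaluable patients, the overall number of patients included will be 56".
- **Analysis of the primary endpoint.** Among 45 evaluable patients, 33 or more with good compliance lead to a positive conclusion, and 32 or fewer to a negative one.

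The secondary objectives report how many patients were offered the study, how many refused, and missing data at each measurement time. None of these puts enrolled never-completers back into the primary denominator, and no analysis of all included patients is stated.

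**The concern.** Entry to the analysis set depends on the behaviour that the endpoint measures. Table 1 places consent, software training and delivery of passwords at enrolment, with the first questionnaire at the first visit. Someone who passes through those steps, starts treatment and completes nothing is a case of REMOQOL not working, and the study exists to count such cases. Removing certain failures from a proportion can only raise it.

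At stake are the primary estimate, the one-sided error rate of the decision rule and the go/no-go conclusion. The Discussion wants to learn whether routine monitoring is feasible outside expert centres and whether patients are receptive to it. A proportion restricted to people who used the system at least once does not answer that.

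**Working it through.** **Inputs.** From Sample size and Analysis of the primary endpoint: p0 = 0.60, p1 = 0.80, one-sided α = 0.05, power 0.90, 45 evaluable patients, cut-off 33, 56 included. The allowance is therefore 56 − 45 = 11 patients. The number of never-completers, k, is not given; I assume a range of 0 to 11.

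**Step 1: reproduce the plan.** With X ~ Bin(45, p):
- P(X ≥ 33 | 0.60) = 0.0446
- P(X ≥ 33 | 0.80) = 0.9005, so β = 0.0995

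The β agrees with the stated 9.9%, and the design is sound for the set it describes.

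**Step 2: a just-passing result, with never-completers counted as failures.** The count stays at 33 and the denominator becomes 45 + k. The one-sided p-value is P(X ≥ 33 | 45 + k, 0.60).

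| k | Proportion | One-sided p |
|---|---|---|
| 0 | 33/45 = 73.3% | 0.045 |
| 1 | 33/46 = 71.7% | 0.068 |
| 3 | 33/48 = 68.8% | 0.137 |
| 5 | 33/50 = 66.0% | 0.237 |
| 11 | 33/56 = 58.9% | 0.621 |

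One never-completer is enough to move a borderline pass above 0.05.

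**Step 3: false-positive rate when compliance among all 56 is exactly 60%.** Removing k never-completers leaves n = 56 − k, and the rate among those left is 0.60 × 56/n. The cut-off c is the smallest with P(X ≥ c | n, 0.60) ≤ 0.05. The false-positive rate is P(X ≥ c | n, 0.60 × 56/n).

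| k | n | c | Rate among those left | False-positive rate |
|---|---|---|---|---|
| 1 | 55 | 40 | 61.1% | 4.9% |
| 2 | 54 | 39 | 62.2% | 8.3% |
| 3 | 53 | 39 | 63.4% | 7.9% |
| 5 | 51 | 37 | 65.9% | 20% |
| 8 | 48 | 35 | 70.0% | 40% |
| 11 | 45 | 33 | 74.7% | 66% |

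The small dip from k = 2 to k = 3 comes from the discreteness of the cut-off. At k = 1 the rate stays just under 5%.

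**Step 4: the rule if all 56 are counted.**
- Cut-off 40: P(X ≥ 40 | 56, 0.60) = 0.0517, too high.
- Cut-off 41: P(X ≥ 41 | 56, 0.60) = 0.0278, and P(X ≥ 41 | 56, 0.80) = 0.9205.

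That 92% needs the 80% alternative to hold in all 56. If 80% was expected only among patients with at least one questionnaire, the all-patient rate is 0.80 × (56 − k)/56, and power at 41/56 becomes:
- k = 1: rate 78.6%, power 87%
- k = 2: rate 77.1%, power 81%
- k = 5: rate 72.9%, power 54%

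**The case against.** The best defence is that never-completers should be few. Eligibility requires patients to be able to complete the questionnaires, training is given at enrolment, a need for help is recorded, and a tablet in the waiting room is an alternative to completion at home. With one to three never-completers, the false-positive rate in Step 3 is between 4.9% and 8.3%. That is a fair point about size, and it stands. It does not change the direction of the bias or give a reason for the condition. The three-month condition may be defended as ensuring enough follow-up to judge compliance. The one-questionnaire condition has no such rationale for this endpoint.

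A second defence is that included minus evaluable patients could be tabulated by reason and the proportion re-expressed afterwards. That is possible without new data, but the stated decision rule would still have been applied to the selected set.

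Three stronger readings are tempting, and the document does not support them:

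- **That all 11 patients in the 20% allowance are never-completers**, so the pass mark is really 58.9%. The same allowance must also cover early death, progression and withdrawal, so this is a ceiling and not an estimate.
- **That patients who drop out of monitoring are replaced instead of counted.** A patient who fills out one questionnaire, stops using the system and meets the three-month condition stays evaluable and can count as a failure. Sample size names drop-out and non-evaluable patients together and does not say that later drop-outs are removed.
- **That the bias is worst in centres that implement the system poorly.** Nothing in the article gives completion by centre.

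**Conclusion.** The point holds. The evaluable definition removes certain failures from the primary proportion and the decision rule, the bias can only favour a positive conclusion, and nothing stated elsewhere corrects it. Its size cannot be fixed from the article. It is negligible if there are no never-completers, modest with one to three, and serious from about five (20%) upward, with 66% as the upper bound. These figures assume true compliance of exactly 60% among all included patients, a cut-off refitted to the patients who remain, and no other exclusions. Independently of those assumptions about the true rate, a single never-completer is enough to take a minimal pass of 33/45 to p = 0.068. The wording should be corrected before the primary analysis.

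**What to change.** Delete the one-questionnaire requirement from the evaluable definition. Count any patient who started sunitinib or pazopanib, had at least one questionnaire due and completed none as not having good compliance. Limiting this to patients with a questionnaire due avoids scoring someone who had no opportunity to complete one. The three-month condition can be left as it is.

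Refit the exact cut-off to the resulting N. If all 56 are included it is at least 41 (α 2.8%). State which population the 80% alternative refers to, and restate the power accordingly: 92% if it refers to this set, less if it was meant only for patients with at least one questionnaire. Report the current evaluable set as a sensitivity analysis.

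The cost is a change of wording and a recomputed cut-off. The reported proportion may be lower. Power falls if the 80% was conditional on some use of the system (Step 4), and in that case the planned 56 may not be enough to keep 90%.

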#### Sample size

The following hypotheses will be tested:

H0 (null hypothesis for inefficiency): 60% or fewer patients having good compliance with REMOQOL during the first 12 months following the initiation of treatment will be considered as irrelevant;

H1 (alternative efficiency hypothesis): 80% of patients having good compliance with REMOQOL during the first 12 months following the initiation of treatment is expected.

Considering Fleming’s One-Stage design [32, 33] with a one-sided α type I error rate of 0.05 and a statistical power of 0.90, it will be necessary to include 45 evaluable patients. Due to an estimated 20% drop-out rate and non-evaluable patients, the overall number of patients included will be 56 (28 per treatment group).

#### Statistical analysis

##### Population description

Baseline variables will be described using the mean and standard deviation for continuous variables and percentages for qualitative variables. Baseline HRQoL scores will be described for each cohort.

##### Analysis of the primary endpoint

Considering the H0 and H1 hypotheses, the α and β parameters previously presented, and Fleming’s one-stage design, it will be necessary to include 45 evaluable patients in the study:If 32 (71%) or fewer patients are found to have good compliance with longitudinal HRQoL completion, the use of REMOQOL will be declared uninteresting in this setting;If at least 33 (73%) patients are found to have good compliance with longitudinal HRQoL completion, the use of REMOQOL will be declared interesting.

The probability of concluding efficacy, when *p* = 60.0%, is α = 0.045%.

The probability of concluding inefficacy, when *p* = 80.0%, is β = 9.9%.

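### The type I error printed for the decision rule, 0.045%, is about 100 times too small; the rule's exact error is 4.5%

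*Protocol article*

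**What the plan says.** Under Sample size, the null hypothesis is that "60% or fewer patients having good compliance with REMOQOL during the first 12 months following the initiation of treatment will be considered as irrelevant", and under the alternative "80% of patients having good compliance with REMOQOL during the first 12 months following the initiation of treatment is expected". The design is Fleming's one-stage design "with a one-sided α type I error rate of 0.05 and a statistical power of 0.90", which leads to 45 evaluable patients.

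Under Analysis of the primary endpoint, the rule is fixed on those 45 patients. The conclusion is negative "If 32 (71%) or fewer patients are found to have good compliance with longitudinal HRQoL completion" and positive "If at least 33 (73%) patients are found to have good compliance with longitudinal HRQoL completion". Two operating characteristics follow. The first is "The probability of concluding efficacy, when *p* = 60.0%, is α = 0.045", printed with a percent sign after the figure. The second is a probability of a negative conclusion at a true rate of 80%, given as β = 9.9%.

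**The concern.** The two error rates stand on consecutive lines, both marked as percentages, and they do not fit together. A rule on 45 patients that separates 60% from 80% with β near 10% cannot also have a false-positive rate of 0.045%. The figure also lies far below the nominal 0.05 to which the design was built.

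The figure matters because this is the trial's only test with a decision rule, and α is its stated chance of declaring the monitoring interesting when true compliance is only 60%. A reader who takes the line literally, or copies it into the results paper, would understate that chance about a hundredfold. The error runs in the trial's favour.

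**Working it through.** **Inputs, all from the protocol article**

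- From Sample size: p0 = 0.60, p1 = 0.80, nominal one-sided α = 0.05, power = 0.90.
- From Analysis of the primary endpoint: n = 45, success if X ≥ 33, failure if X ≤ 32, stated α = 0.045% (0.00045 as a proportion), stated β = 9.9%.

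**Step 1: the figures that should reproduce**

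With X binomial(45, p), β = P(X ≤ 32 | p = 0.80) = 0.09945, or 9.9%. This matches the printed β. Power is 1 − 0.09945 = 0.9005.

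The sample size also reproduces. For each n, take the smallest boundary with exact α ≤ 0.05:

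| n | Success if X ≥ | Exact α | Exact power |
|---|---|---|---|
| 42 | 31 | 0.0449 | 0.882 |
| 43 | 32 | 0.0354 | 0.864 |
| 44 | 33 | 0.0277 | 0.846 |
| 45 | 33 | 0.0446 | 0.901 |

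No n from 30 to 44 reaches power 0.90 under this constraint, so 45 with a boundary of 33 is the smallest exact design.

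**Step 2: the type I error**

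α = P(X ≥ 33 | p = 0.60) = Σ C(45, k) 0.6^k 0.4^(45−k) for k = 33 to 45.

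| k | Probability |
|---|---|
| 33 | 0.02304 |
| 34 | 0.01220 |
| 35 | 0.00575 |
| 36 | 0.00240 |
| 37 | 0.00087 |
| 38 to 45 | 0.00037 |
| Sum | 0.0446 |

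The result is 4.46%, or 4.5% to one decimal. Against the printed value, 0.0446 / 0.00045 ≈ 99. In odds, 1/0.00045 ≈ 2,200 and 1/0.0446 ≈ 22.

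The probability of success rises with p, so 4.46% is also the largest false-positive rate over the whole null hypothesis (60% or fewer).

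**Step 3: can another reading give 0.045%?**

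- *Normal approximation.* The mean is 45 × 0.60 = 27 and the SD is √(45 × 0.24) = 3.286. With continuity correction, (32.5 − 27)/3.286 = 1.67 gives 4.7%. Without it, (33 − 27)/3.286 = 1.83 gives 3.4%.
- *A different boundary at n = 45.* A boundary of 37 gives α = 0.124% with power 44.1%. A boundary of 38 gives α = 0.037% with power 29.7%. Neither agrees with the printed boundary or with β = 9.9%.

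No variant tried gives 0.045%. The proportion 0.045 with a percent sign added explains the figure exactly.

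**The case against.** The strongest reply is that nothing depends on this line. Sample size gives the design level correctly as a "one-sided α type I error rate of 0.05 and a statistical power of 0.90", and the analysis section refers back to those parameters. A statistician who sees 0.045% beside β = 9.9% on 45 patients will recognise the slip and read 0.045. Correcting it alters no sample size, boundary, analysis or conclusion. It is also loose to say that a positive result would look a hundred times more certain, because α is a property of the rule before the data and not the certainty of a given result.

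All of this stands as to weight and wording. Sample size contains no error; it is the statement that the printed α contradicts. The accurate claim is that the stated false-positive rate is too low by a factor of about 100. None of it makes the printed figure right. The line is a complete statement about the primary analysis, not a detail left to a longer document, and not every reader will check it against the design section.

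**Conclusion.** The point holds. The stated α of 0.045% is wrong as printed; the exact value for the stated rule is 4.46%, about 99 times larger. It is a unit error and not a design error: n = 45, the 32/33 boundary, the nominal one-sided 5% level, β = 9.9% and the decision rule all stand. It should be corrected because it misstates, in the favourable direction, the error rate of the trial's only formal decision rule.

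The calculation assumes what the one-stage design assumes: exactly 45 evaluable patients, each an independent success or failure with a common probability.

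**What to change.** Under Analysis of the primary endpoint, replace the printed α with 4.5%, which matches the scale of the β beside it, or write 0.045 without the percent sign. Leave β = 9.9% and everything else in the design unchanged. If the full protocol or an analysis plan carries the same line, correct it there too, so that the wrong value does not reach the results report.

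The cost is one figure. The stated error rate becomes less favourable but remains below the nominal 5%.
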